### MNI intervention description

The MNI intervention consists of four biweekly sessions that last approximately 45–60 min and consist of two parts: a network interview with closed-ended network questions and a discussion of resulting network visualizations conducted using a MI approach. Structured network interview questions will be similar to previous studies with homeless populations [6–8, 41, 43, 76, 77]. Participants will be asked to identify people they have had contact with in the past 2 weeks, with follow-up questions about each of these contacts (e.g., likelihood that they will drink alcohol or use drugs in the next 2 weeks, if the participant drank more alcohol or used more drugs than they wanted to when with the contact; if the participant has had unprotected sex with any of the contacts in the past 2 weeks; whether any of the contacts provide social support to the participant; whether the contacts interacted in the past 2 weeks). As the participant talks, the facilitator will enter the participant’s interview responses into the computer-assisted interface, which will subsequently generate several social network visualizations based on the participant’s responses. See Fig. 2 for examples of network visualizations for a hypothetical MNI participant. These visualizations are intended to provide content for discussions during the MNI. The facilitator would show the diagram and then use MI techniques (e.g., asking evocative open-ended questions, stating reflections, elaborating on change talk) to discuss what patterns the participant notices in the diagram (e.g., how certain contacts may trigger their AOD use and how they feel about those contacts). For the example shown in Fig. 2, in Session 1, the facilitator would gather information by stating “Tell me about the different groups of people you see” and “The red circles are people you said you tend to drink more with, tell me about those people.” The facilitator would use MI techniques to explore and resolve any ambivalence about changing their AOD and risky sexual behaviors.

**Fig. 2 Fig2:**
[figure not shown]
Hypothetical MNI participant network visualizations across two sessions. *Each diagram* demonstrates network members (“alters”) with *circles* (“nodes”) and *lines* (“edges”) connecting alters who have interacted with each other in the past 2 weeks. The *left* hand diagram (Session 1) depicts a network of ten nodes with two separate groups (“components”) and one network member who had no interactions with other alters (an “isolate”). One component in Session 1 is comprised of all AOD users and the other includes no AOD users. The *right* hand diagram shows that three of session 1 network members are no longer part of the network and three new members have been added to the network

The second–fourth sessions are designed to build on previous discussions. Facilitators will start these sessions with a discussion of the goals identified in the previous session by asking, “Tell me how those goals have been going for you. Have things changed? Did anything get in the way?” After discussion of the goals, the session will include all of the same questions about the participant’s network they were asked in the previous sessions, including a discussion of the current and previous visualizations. For the example shown in Fig. 2, in Session 2, the facilitator might ask “What differences do you see between this week’s diagram and our first one?” The facilitator would highlight any change talk about the new people in their network who do not use AOD (i.e., changes in network structure) and the strategies they used to change their network composition (e.g., fewer who are using AOD). The facilitator would also explore whether the participant is willing to interact less with the two remaining people who do use AOD in their network.

This four session strategy will allow time for network change strategies to be put into place and for participants to discuss change experiences with the intervention facilitators. For example, participants may discuss wanting to spend more or less time with network contacts, wanting to connect network members who do not know each other, or ties to network contacts that they would like to break. Participants may not be able to put strategies to achieve these goals in place right away or they may need to try different strategies. Initial changes in network structure or composition may trigger the opportunity to develop strategies for secondary or tertiary changes. Also, participants may require encouragement from facilitators to maintain initial strategies. Four sessions will allow ongoing discussions of this process. Also, some of their strategies may produce unexpected negative results and they will be able to discuss these unexpected effects with facilitators who can help them develop alternative strategies. In summary, the visualizations resulting from the network interview are designed to provide both intervention facilitators and participants with a tangible object to focus questions and answers and make abstract discussions of social life, relationships, and social change more concrete.

### Usual care

Participants assigned to both the intervention and control conditions will receive usual case management support provided by SRHT and SRO Housing. After an initial case management intake assessment that is scheduled to occur within the first 30 days that a resident is housed, residents are expected to meet with case managers regularly for up to 60–90 days, based on need. Case management meetings last 15–60 min and are customized to the residents’ needs. Case managers facilitate residents’ access to on-site services, such as support groups, as well as make referrals to offsite services.

### Intervention fidelity monitoring and measurement

Intervention facilitators will be trained in MI techniques and a clinical psychologist affiliated with the motivational interviewing network of trainers (MINT) will review the recording of each session to provide regular feedback and re-training, as necessary. Fidelity to the intervention protocol will be assessed with an 8-item scale to determine if key components of the intervention were discussed, similar to previous studies [78–80]. The fidelity checklist will consist of a five-point Likert scale with response options ranging from “completely”, “partially”, to “not at all” covered. For example, items will assess whether the facilitator discussed the client’s desires to make network changes, such as interacting with specific network ties more or less frequently.

### Measures

Table 1 gives an overview of the pilot study measures and the phase in which they will be assessed. Study measures were selected based on their use in similar populations, including low income, low education AOD using populations [81, 82] and populations engaging in heavy AOD use and high-risk sexual behavior [83]. Many of the measures have also been recommended by the VA Mental Health QUERI taskforce [84] and NIDA [85]. Because of the pilot nature of this study, only one follow-up assessment will be conducted. We plan to assess participants within 2 weeks after the final MNI session in order to measure the immediate benefits of the intervention rather than longer-term effects. The assessments will be collected in a one-on-one in-person interview by an independent data collection organization using EgoWeb as a computer-assisted personal interviewing (CAPI) software. The data collectors will be blind to the study condition assigned to the participant.

**Table 1 Tab1:** Study measures and administrative timeline

	Screening	Baseline	Follow-up
At-risk drinking: AUDIT-C	X		
Any illegal drug use: DAST	X		
Demographics: age, gender, race/ethnicity, education		X	
Lifetime experience with homelessness		X	
Recent experience with homelessness		X	X
Readiness to change: RTCQ, RTCQ-SB, contemplation ladders		X	X
Self-efficacy: AASE, condom efficacy		X	X
AOD use: Quantity Frequency Index (QFI)		X	X
High-risk sex: unprotected sex, concurrent partnerships		X	X
Social network: composition and structure of drinking/drug/abstinent supportive network members		X	X
Client satisfaction (MNI participants only)			X

### Baseline measures

We will assess baseline *demographic characteristics* (i.e., age, gender, race/ethnicity, education, number of children, marital status, income) and history with homelessness to describe the study population, explore whether there are any differences between the participants assigned to the different study conditions, and potentially explore as potential intervention effect moderators.

### Outcome measures

We will measure both proximal and distal outcomes. Proximal outcomes are readiness and self-efficacy to change AOD use and safe-sex behavior, and social network composition and structure. Distal outcomes are AOD use behaviors and HIV risk behaviors. For the proximal outcomes, we will measure readiness to change in two ways. The first method is a one-item *contemplation ladder* adapted from the smoking literature [86] that displays a picture of a ladder with corresponding stages of change. For the substance that the participant considers their biggest current problem, they are asked to identify where they are in changing their use of the substance on a 0–10 scale (e.g., 0 = “No thought of quitting”, 5 = “Think I should quit but not quite ready”, 10 = “Taking action to quit”). A separate ladder will ask participants to give a similar rating of their willingness to change their unprotected sex behavior. The ratings that these ladders produce have adequate reliability and good validity [86] and have been used for smokers with schizophrenia [87], drinking adults with multiple sex partners [83], and welfare applicants [81]. We will also measure readiness to change using the Readiness to Change Questionnaire (RTCQ) [88–90], which consists of 12 items that assess the readiness to change AOD use (precontemplation, contemplation, preparation, or action) and the Readiness to Change Risky Sexual Behavior (RTCQ-SB) scale, which consists of 11 items adapted from the RTCQ for safe-sex behavior [83]. We will measure self-efficacy using an abbreviated version of the Alcohol Abstinence Self-Efficacy Scale (AASE), [91] which consists of five items indicating how confident participants feel in their ability to abstain when depressed, relaxed, craving substances, and offered alcohol. We will measure *self*-*efficacy to use condoms* with an instrument that has shown good reliability and concurrent validity [92] and has predicted unprotected sex in homeless populations [41, 43, 93].

We will collect *social network* data similar to previous homeless studies to measure change in network composition and structure [6–8, 43, 94–96]. Participants will be asked to name 20 network contacts (“alters”), who are at least 18 years of age, during the baseline and follow-up assessments because a minimum of 20 alters is necessary to produce unbiased estimates of network structure [97, 98] and to measure network composition [7]. Participants will be asked questions about the demographics of each of these network alters (gender, recent and lifetime homelessness), the drinking/drug use/safe-sex behavior of each alter, their relationships with each alter (emotional closeness, frequency of contact), and the relationships between each pair of alters [e.g., “Does (Alter 1) know (Alter 2)?”]. Based on aggregating questions about the social support provided by each alter, we will construct measures that are similar to measures of *Perceived Social Support* [36, 99] (i.e., the number and/or proportion of network members who provide emotional support, advice, tangible support) and measures that result from the *Important People Drug and Alcohol interview*, in which network members are rated on relationship characteristics (e.g., emotional closeness), drinking, drug use, safe-sex behavior, and their influence on the participants’ own high-risk behavior [100].

For the distal outcomes, we will use self-reported AOD use as our primary AOD use measure. At each assessment we will assess alcohol drinking frequency (never, once a month, 2–4 times a month, 2–3 times a week, 4–5 times a week, 6 or more times a week) and drinks per drinking day (typical number of drinks when drinking). For drug use, we will assess frequency of past 30 day drug use (none, once, twice, three times, once a week, twice a week, 3–4 times a week, 5–6 times a week, every day) for each of the following: marijuana, cocaine, crack, heroin, amphetamines/methamphetamines, injection drugs, drugs typically requiring a prescription “on their own”, and any other drug to get high or feel good. Frequency and intensity of use are thought to represent independent dimensions of AOD use behavior and tend to be relatively uncorrelated, making them a good choice as outcome measures [101]. We will derive a Quantity Frequency Index (QFI), which has a history of reliability and validity across various populations [102].

To measure *HIV risk behaviors*, we will ask about the respondent’s sexual behavior in the past 30-days overall and with particular partners named as alters. We will ask them how many times they had sex (vaginal or anal) and how often they used condoms when they had sex. We will also ask if they were engaging in sex with other partners concurrently. We have used these measures in studies of HIV risk among homeless women [43], youth [41], and men [93, 103].

To measure network changes, we will construct measures of how central various network members are using standard social network centrality measures [104, 105] similar to other studies of the social networks of homeless populations [6–8, 41, 43, 76, 77]. For example, we will measure *degree centrality* for each network member which is a count of the number of people connected to that network member in the network. We will also measure centrality with other measures that have been found to be associated with unprotected sex in homeless populations, such as *betweenness centrality* (a continuous measure of how often an alter lies on the shortest path between pairs of other alters in the network) [40] and *closeness centrality* (a continuous measure of how directly or indirectly connected a particular alter is to all the other members of a network) [77]. We will also calculate measures of network composition and size to determine if the intervention is associated with changes in the types and quantities of people in the network. For example, we will calculate proportion of alters who are drug users, who are supportive, who are perceived to engage in risky sex, etc. We will also calculate measures of overall structural characteristics to determine if the intervention affected overall interaction among network members. For example, we will calculate *density* at both time points. Density is an index that represents the proportion of ties that exist in a network relative to the total number of possible ties, and varies from 0 to 1. We will also calculate *centralization*, which is another index between 0 and 1 that measures the degree to which one or a few individuals in the network maintain the majority of ties.

During the post-intervention assessment, MNI participants will answer 23 questions about the quality of and their satisfaction with the MNI sessions they attended on a five-point Likert scale, with a higher score representing higher quality and satisfaction (e.g., I feel that the things I did in the sessions will help me to make the changes that I want; The different activities we did in the sessions were helpful; The facilitator valued my opinion; The different activities we did in the sessions were helpful). Similar satisfaction questions have been used in prior research [106–108].

### Analyses

Given the planned sample size (i.e., n = 60), sophisticated modeling and adjustments for non-response might not be possible, and the bulk of the analyses will be primarily descriptive. We will estimate the outcomes’ variability in this population and more generally assess the hypothesized trends to determine the intervention promise and identify potential mediators for future studies. Analyses will use the standard intent-to-treat (ITT) approach to examine the effect of offering the MNI intervention to eligible and consented participants. We will attempt to follow up with all participants, regardless of their MNI participation. Our ITT approach will analyze participants as belonging to the group they were randomized to, regardless of their compliance, because excluding those who do not complete the MNI would bias results in favor of MNI, increasing type I errors [109].

We will be able to obtain intervention effect estimates on both the proximal (i.e., efficacy and readiness to change AOD, safe-sex behavior, and networks) and distal outcomes (i.e., AOD use and HIV risk behavior) using a difference in differences (DID) approach [110]. The DID approach is well-suited to the data generated by the adopted study design: for every subject we will have a pre- and post-intervention observation and a randomized group indicator (intervention or control). We will implement the DID approach by fitting a mixed-effects model in which participants are treated as random effects while time, the intervention group indicator, and their interaction are treated as fixed effects. This modeling approach accounts properly for the two repeated measures’ correlation on each participant and tends to produce efficient intervention effect estimates [111]. The intervention effect estimate is given by the coefficient of the interaction between the time and intervention indicators.

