### Study design, aims and hypotheses

This study was designed to explore whether employing a MI approach to present personal network information electronically would help HF residents transition away from high-risk social networks and toward low-risk, supportive social networks and result in less risky AOD use and sexual behaviors. Consistent with the stage model approach to behavioral therapy intervention development [69], the study consists of two phases, a development phase (i.e., Stage 1a) and a pilot test phase (i.e., Stage 1b). The Stage 1a development work has been completed and consisted of developing and iteratively testing the intervention to assess usability, feasibility and acceptability among residential support services staff and HF residents. Data analysis of qualitative data generated during Stage 1a is ongoing and will be reported elsewhere. This paper describes the design of the Stage 1b pilot test of the intervention.

The aim of the pilot study is to generate preliminary evidence about the effectiveness of the intervention on reducing AOD use and HIV risk behaviors. To meet this aim, 60 residents with past year harmful AOD use will be randomly assigned to receive the intervention or usual care. The justification of a sample size of 30 per study condition is based on published guidelines for conducting Stage 1b clinical trials which are considered pilot studies, developmental in scope, and exploratory in nature [69]. We will analyze baseline (i.e., pre-intervention) and follow-up (i.e., post-intervention, approximately 90 days from baseline) data to determine the feasibility, acceptability and promise of the intervention for a subsequent Stage 2 efficacy trial [69].

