### Randomization

After participants complete the baseline assessment, they will be assigned to one of two experimental conditions (i.e., intervention or control). We aim to randomly assign 60 participants using a stratified permuted block randomization strategy. Given the relatively small sample size, the randomization might produce an unbalanced assignment with respect to gender. For this reason the randomization will be stratified. About 26 % of SRHT clients are women and stratifying on this characteristic will ensure an approximately equal number of women assigned to both conditions. If the intervention and control groups turn out to be unbalanced with respect to other characteristics, we will use covariate adjustment at the analysis phase. Next, participants assigned to the intervention arm will be contacted by project staff by phone to schedule the four MNI sessions, one every 2 weeks. If the participant is difficult to reach by phone, a project staff member will attempt to contact the participant by visiting their residence to schedule their first session. Participants will be provided with appointment cards as reminders. Participants will be given a $5 food gift card for each intervention session they attend.

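### The planned time-by-group interaction estimates a baseline group difference that randomisation already sets to zero, so it is less precise than a baseline-adjusted analysis of the same data

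*Protocol article*

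**What the plan says.** The protocol article, Analyses, adopts a difference-in-differences approach for the proximal and distal outcomes. It is fitted as a mixed model with participants as random effects, in which "time, the intervention group indicator, and their interaction are treated as fixed effects". The estimator is fixed explicitly: "The intervention effect estimate is given by the coefficient of the interaction between the time and intervention indicators". The section expects two measurements per person: "for every subject we will have a pre- and post-intervention observation and a randomized group indicator". It adds that the approach "accounts properly for the two repeated measures" (the text goes on to name their correlation) and "tends to produce efficient intervention effect estimates".

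The Randomization section gives the order of events: "After participants complete the baseline assessment, they will be assigned to one of two experimental conditions". It stratifies on gender and allows covariate adjustment only if the arms turn out unbalanced on other characteristics. It does not name the baseline value of the outcome as a covariate.

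**The concern.** Difference in differences is built for comparisons in which the groups may truly differ before treatment, so that this difference has to be removed. In this trial the baseline is taken before allocation, so any baseline difference between arms is chance. A model with a free group main effect estimates that chance difference and subtracts all of it from the follow-up difference. Unless baseline and follow-up move one for one, this subtracts too much and adds variance.

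With 30 per arm and a sample size taken from pilot guidelines, precision is scarce. The effect estimates and their intervals are what will be used to judge whether the intervention shows promise for a Stage 2 trial. The same estimator is planned for the proximal and distal outcomes alike, so any loss recurs across them.

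**Working it through.** The article states no standard error, power, SD or correlation, so there is no figure of its own to reproduce.

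**Inputs**
- n = 30 per arm, from Study design, aims and hypotheses: "60 residents with past year harmful AOD use will be randomly assigned to receive the intervention or usual care" and "The justification of a sample size of 30 per study condition is based on published guidelines".
- One baseline and one follow-up value per person (Analyses), with baseline before allocation (Randomization).
- r, the baseline to follow-up correlation: not given. Assumed 0.3 to 0.8.
- Outcome SD σ: not given. Results are in units of σ, with equal SDs at both times until step 6.

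**Step 1: what the coefficient is.** With complete data the interaction equals (mean change, intervention) minus (mean change, control). In a simulated data set of 30 + 30, the fitted coefficient and the difference in mean change were both 0.3655.

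**Step 2: variances.**
- Planned: a change score has variance 2σ²(1-r), so the difference between arms has variance 2 × 2σ²(1-r)/n = 4σ²(1-r)/n.
- Baseline-adjusted (common baseline mean, or baseline as covariate; large-sample form): 2σ²(1-r²)/n.
- Ratio, adjusted to planned: (1-r²)/[2(1-r)] = (1+r)/2. The loss is therefore (1-r)/2.

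**Step 3: numbers with n = 30, σ = 1.** The last column is 60(1+r)/2, the number of participants which, analysed with baseline adjustment, would give the precision of the planned analysis of 60.

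| r (assumed) | Variance, planned | Variance, adjusted | Variance falls by | SE, planned | SE, adjusted | SE falls by | 60 planned equals |
|---|---|---|---|---|---|---|---|
| 0.3 | 0.0933 | 0.0607 | 35% | 0.306 | 0.246 | 19% | 39 |
| 0.5 | 0.0667 | 0.0500 | 25% | 0.258 | 0.224 | 13% | 45 |
| 0.7 | 0.0400 | 0.0340 | 15% | 0.200 | 0.184 | 8% | 51 |
| 0.8 | 0.0267 | 0.0240 | 10% | 0.163 | 0.155 | 5% | 54 |

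At r = 0.5 the 95% interval half-width (multiplier about 2.00) goes from 0.52σ to 0.45σ. Outside the assumed range the variance loss is 50% at r = 0 and 5% at r = 0.9.

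**Step 4: against ignoring baseline.** Comparing follow-up means alone has variance 2σ²/n = 0.0667. The planned variance 4σ²(1-r)/n exceeds this whenever r < 0.5; at r = 0.3 it is 0.0933.

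**Step 5: check by simulation.** In 20,000 trials of 30 + 30, regression on group and baseline reduced the variance by 33%, 24% and 8% at r = 0.3, 0.5 and 0.8. This is slightly less than the formula, because the baseline slope has to be estimated. Both estimators were centred on the true value.

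**Step 6: unequal SDs.** With k the follow-up SD divided by the baseline SD, the loss is 1 - k²(1-r²)/(1+k²-2rk). For k from 0.7 to 1.5 and r from 0.3 to 0.8 it runs from about 0% (for example k = 1.5, r = 0.65) to 58% (k = 0.7, r = 0.3).

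**Step 7: chance imbalance.** The chance baseline difference has SD √(2/30) = 0.26σ. Given a difference D, the planned estimate is off by (1-r)D on average. For an imbalance of one SD at r = 0.5 that is 0.5 × 0.26 = 0.13σ. Averaged over randomisations it is zero.

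**The case against.** The strongest case for leaving the plan alone has five parts.

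- **The estimator is valid.** A reader might infer that the planned effect is biased. The documents do not support that: under randomisation the difference in mean change is unbiased, and step 7 describes an error conditional on an observed imbalance. This objection stands in full.
- **This is a pilot.** The article calls the study exploratory and the analyses mainly descriptive, and no power, precision target or progression threshold depends on this standard error. That limits the importance, but interval width still matters for a descriptive effect estimate, and the improvement is free.
- **The efficiency remark is hedged.** A reader might infer that the article makes a false claim. It says only that the approach "tends to produce efficient intervention effect estimates", in the same sentence as the within-person correlation, and does not claim the most efficient estimator. It can be read as a comparison with ignoring that correlation. The wording is loose, not shown to be wrong.
- **The figures are conditional.** A reader might take 10% to 35% as the loss in this trial. It is a variance-scale range that requires r between 0.8 and 0.3, equal variances and a continuous outcome. Several outcomes are ordinal frequencies, counts or proportions, to which the formula does not carry over directly.
- **Change matches the hypothesis.** The behavioural hypothesis is worded as reductions between baseline and follow-up. But with equal expected baseline means, the difference in mean change and the difference in follow-up means are the same quantity, so the adjusted analysis answers the same question.

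One further inference should be avoided: the planned model does not drop participants who have only a baseline. A mixed model already keeps them, so this is no advantage of the constrained model over the plan.

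**Conclusion.** The point holds as one of avoidable imprecision. The article fixes a free group main effect although its own order of events makes the expected baseline difference zero. For continuous outcomes with equal variances at both times, the information lost is (1-r)/2. Over an assumed r of 0.3 to 0.8 this is 35% down to 10% on the variance scale, or about 19% down to 5% on the standard-error scale. If r is below 0.5, the planned analysis is less precise than one that ignores baseline altogether. Since r and the SDs are not in the article, the size for any particular outcome is unknown, and with unequal SDs the loss can be close to nil or larger than these figures. The planned analysis remains valid; it is simply not the best use of 60 participants.

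**What to change.** For outcomes analysed with a linear model, do one of the following:

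- keep the mixed model but drop the group main effect, so that the fixed effects are time and time-by-group with a common baseline mean, and let the covariance over the two times be unstructured; or
- regress the follow-up value on group and the baseline value of the same outcome.

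Report the adjusted group difference at follow-up as the effect. For discrete outcomes, include the baseline value as a covariate in a model suited to the outcome. Make this adjustment part of the plan for every outcome measured at baseline, and do not leave it to depend on observed imbalance.

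Either say that the efficiency remark refers to handling the within-person correlation, or remove it.

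The cost is a few sentences in Analyses and a changed model specification: one term fewer and, in the mixed model, a freer covariance. No new data, visits or participants are needed.
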